**Exclusion criteria:**
Diagnosed with organic or substance-induced psychosisLack of capacity to provide informed consentUnsafe to participate in research as viewed by their treating clinician (ie, clinically unstable or at risk for self-harm or harm to others)

### Recruitment

Participants were recruited from Beijing Anding Hospital, which is a major tertiary psychiatric hospital located in Beijing, China. Participants were initially approached by a clinician working at the hospital to introduce the project and assess the willingness and potential eligibility of the potential participant to participate in the study. If participants appeared to be eligible and willing to participate, they were referred to the principal researcher who confirmed their eligibility. When eligible, potential participants were given a participant information sheet to read, and their contact details were obtained by the researcher with their consent. The principal researcher followed up with a phone call to the potential participant after at least 48 hours to explain the details of the study and answer any questions that the potential participant had about the study. If the potential participant was still interested in taking part, a face-to-face meeting was arranged to obtain written consent to participate using a hard copy consent form prior to conducting the baseline assessment at the same meeting. Participants were recruited until the recruitment target was met (n=40).

### Study Intervention and Procedures

YouXin is a smartphone app designed to facilitate symptom self-monitoring for people with psychosis. The app is adapted from the ClinTouch app [13], a self-monitoring app for psychosis validated against the Positive and Negative Syndrome Scale (PANSS) and the Calgary Depression Scale for Schizophrenia (CDSS) items. The PANSS and CDSS have been translated and validated in Chinese and have been widely used in practice in China [43,44]; however, app-based versions of these measures among people with psychosis have not been validated in Chinese. In this study, we translated the ClinTouch-based PANSS and CDSS items into Chinese and combined these items with passively collected data to develop the YouXin app to be tested in the Chinese context. Screenshots of the YouXin app are shown in Figure 1.

**Figure 1 figure1:**
[figure not shown]
Screenshots of the app prototype: (A) log-in page, (B) user center, (C) assessment module.

The YouXin development team consisted of experts from various disciplines, including academics, clinicians, software engineers, and experts by experience. The principal researcher led the development of the app and was supported by members of the research team who are academic clinicians at the University of Manchester (a Professor of Clinical Psychology and a Professor of Adult Psychiatry). A psychiatrist at Beijing Anding Hospital assisted the development of the app to ensure the content reflected the Chinese context. A technology team led by a computer scientist at Beijing Jiaotong University supported software development.

To maximize the usability and acceptability of the app for end users (ie, service users and clinicians), the development process utilized a systematic coproduction approach. A series of coproduction consultation meetings was conducted by the principal researcher with service users and clinicians at Beijing Anding Hospital. We used an iterative approach to coproduction, which means the outputs of a previous meeting formed the content of subsequent consultation meetings. The framework for coproduction (shown in Figure 2) was inspired by the process of development used for the Actissist app [45,46], a cognitive behavioral therapy–informed app designed to support people in the early phase of psychosis, and the UK government user research guidelines [47]. A series of participatory design consultations involving 3 phases (alpha, beta, and live phases) was held with service users with severe mental health problems and clinicians. As the YouXin app is adapted from the ClinTouch app, we skipped the discovery phase, which is normally used to generate ideas and hypotheses for a completely new product. The remaining 3 phases are described in Textbox 2.

**Figure 2 figure2:**
[figure not shown]
The coproduction process.

The phases of the coproduction process.Alpha:The alpha phase aims to understand the end users’ (clinicians and service users) needs for using digital tools to monitor symptoms and demonstrate the preliminary design with users (the ClinTouch app and the user interface prototypes of the YouXin app). The design, contents, and functions of the app were further developed based on the feedback from users.Beta:The principal researcher and software engineer integrated the feedback and delivered a functional prototype that users could install on their phones. During the meeting, users tested the app and provided feedback.Live:A fully developed digital platform was presented to users (3 clinicians and 3 people with psychosis) to try out for a week. This meeting focused on evaluating the usability and acceptability of the app and any major issues regarding implementation.

YouXin has 2 core functions: active monitoring of symptoms (ie, smartphone survey) and passive monitoring of behavioral activity (ie, passive data collection via embedded smartphone sensors). The app is available for both Android and iOS platforms. The active monitoring uses a time-contingent design. To minimize participant assessment burden and increase compliance, in accordance with a previous similar study [38], prompts were set to alert at 2 pseudorandomized timepoints per day, during a 12-hour interval from 10 AM to 10 PM, 7 days a week for 4 weeks. A minimum 1-hour increment was set between each prompt on a particular day to avoid clustering of responses. Participants could either snooze (5 minutes or 30 minutes) or decline answering the prompt. Based on previous works by the research group, on average, it takes 70 seconds to complete each prompt. Smartphone sensors passively collected GPS data every 5 minutes. According to a recent systematic review [39], passive sensing was feasible for measuring negative symptoms; specifically, GPS indicators were associated with apathy, avolition, asociality, and anhedonia [48,49]. All collected data were uploaded to a secure server at Beijing Anding Hospital.

Participants were given a training session by the principal researcher to help them navigate the app after they consented to take part. During the training, the principal researcher helped the participant download the app onto their smartphone and gave a demonstration of the app. Participants had the opportunity to practice using the app and ask questions during the process; they had access to the app from the training session until the 4-week timepoint. An opt-out approach was applied to give participants autonomy to switch on or off the passive sensing section during the study.

The principal researcher provided technical support as needed during the study; no clinical care was provided by the research team (clinical care continued as usual from the service). The participant was referred to their treating clinician for appropriate mental health care should any clinical issues be raised to the research team. Participants were informed at the training sessions that the app is not suitable for seeking urgent medical care while in any emergency circumstance.

### Data Collection

The timeline of outcome assessments is summarized in Figure 3. Participants were assessed in an in-person meeting at baseline, 1 week after baseline, and 4 weeks after baseline. To assess the validity of the remote monitoring, PANSS and CDSS were assessed at 1 week to calculate the association between the active and passive monitoring results and relevant domains of the clinical assessment. To determine which outcomes are sensitive to change in this population, participants were asked to complete an assessment of relevant outcomes of the self-monitoring intervention at baseline and the 4-week timepoint. The assessor is a clinician, has been trained in the assessment measures used, and has rich experience in conducting assessments in clinical trials. Semistructured qualitative interviews were conducted after the 4-week timepoint to explore the acceptability of the app.

**Figure 3 figure3:**
[figure not shown]
Timeline of data collection. CDSS: Calgary Depression Scale for Schizophrenia; MINI: Mini International Neuropsychiatric Interview; PANSS: Positive and Negative Syndrome Scale; PHE-S, Patient Health Engagement Scale; PSP, Personal and Social Performance; QFQ: quantitative feedback questionnaire; SIPS: Structured Interview for Prodromal Syndromes.

### Outcome Measures

#### Sociodemographic and Clinical Characteristics

Sociodemographic characteristics including age, gender, education level, marriage status, average income, accommodation and living situation, employment status, and ethnicity were collected. We also collected data regarding digital literacy and mental health literacy.

#### Data From Service Users’ Electronic Health Records

Number of hospitalizations, time at first onset, number of episodes, and medication(s) or therapy used before and during the study were collected from service users’ electronic health records (EHRs). At Anding Hospital, the EHR is used in both outpatient clinics and inpatient units and is shared within the hospital. All records are kept in the EHR system using computers, and no records are written by hand; service users receive a hard copy of their record following each appointment.

#### Clinical Measurements

The Chinese version of the Mini International Neuropsychiatric Interview [50,51] was used to determine the DSM-5 diagnosis.

The Chinese version of the Structured Interview for Prodromal Syndromes [52,53] was used to assess the risk for psychosis.

Psychotic symptoms were rated using the Chinese version of the PANSS [54,55], a 30-item scale that assesses positive symptoms, negative symptoms, and general psychopathology. The Chinse version is comparable to the original version and has good internal consistency reliability (Cronbach α=.87) [43].

Mood symptoms were assessed using the Chinese version of the CDSS [56,57], a 9-item scale designed specifically for assessing depression for schizophrenia. The Chinese version [44] has good reliability (Cronbach α=.798-.810) and is significantly correlated with the Hamilton Depression Scale (r=0.76) and PANSS-G6 (r=0.70).

Service user engagement was measured using the Chinese Version of the Patient Health Engagement Scale [58], a self-report scale assessing service users’ attitudes toward engagement in health care.

Social functioning was rated using the Chinese version of the Personal and Social Performance scale (PSP) [59,60], a 100-point single-item rating scale assessing 4 main areas of functioning, including socially useful activities, personal and social relationships, self-care, and disturbing and aggressive behaviors.

Quality of life was evaluated using the Chinese version of the EQ-5D-5L [61], a self-report questionnaire designed to assess health status and health-related quality of life. The EQ-5D-5L consists of 5 questions that assess 5 health dimensions and a visual analog scale to assess the overall current health judged by the individual respondents.

#### Smartphone Monitoring

##### Active Monitoring

Active monitoring consisted of the following 3 sections: psychotic symptoms, mood symptoms, and contextual information. The psychotic and mood symptom items were translated into Chinese from the ClinTouch app and were compared against the Chinese version of the PANSS and CDSS. Contextual questions were added to understand the context of participant responses and to validate GPS data. Examples of the items are shown in Table 1.

**Table 1 table1:** Examples of the active monitoring items.

Domain	Item	Response items	Format
Psychotic symptoms	“I have heard voices.”	1-7	Likert scale
Mood symptoms	“I have felt sad.”	1-7	Likert scale
Contextual questions	“Where were you?”	At home; at work; at school or other educational setting; in hospital; in vehicle; in a convenience store, supermarket, or shopping mall; outside walking; inside other; outside other	Check box

##### Passive Monitoring

Passive monitoring used collected GPS data to measure mobility and activity level of users. GPS mobility indicators measured on the smartphone, including home time, distance travelled, and location clusters, will be extracted following the procedures by Müller et al [62]. Briefly, locations will be clustered as “unique” if a person spent at least 30 minutes within a 200-meter radius. Home location will be determined by selecting the mode of location clusters during the night (ie, 9 PM to 6 AM). Distance travelled will be computed by aggregating the distance changes between 2 successive GPS data points; however, distance changes of GPS data points in the same location cluster will be considered as zero. Time spent at each location, including time at home, will be calculated by summing the differences of the time stamps of 2 successive GPS data points in the location cluster.

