### Study Setting

The study took place at Beijing Anding Hospital of Capital Medical University, which is one of the largest tertiary psychiatric hospitals in the Beijing metropolitan area. The hospital has 800 beds, an average 5000 inpatient admissions per year, and over 1200 daily outpatient visits.

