#### Validity

The validity of active monitoring items will be assessed against relevant clinical assessments (ie, PANSS and CDSS) using Spearman correlation. An exploratory analysis will also be conducted to understand the association between mobility indicators, corresponding contextual questions in active monitoring, and PANSS negative symptom scores. We define a moderate statistically significant correlation (ie, Spearman rho>0.35) as the validity threshold.

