### Statistical Analysis Plan

All quantitative analyses will be performed using R (version 4.0.5) [66]. Feasibility data and safety data including (1) recruitment and retention data, (2) app usage data, (3) completeness of study measures, and (4) the number and nature of adverse events will be analyzed using appropriate descriptive statistics (mean and standard deviations for continuous data; counts and percentages for categorical data). Logistic regression and linear regression analyses will be used to explore sociodemographic and clinical characteristics and device attributes as predictors of feasibility (eg, dropouts, app usage).

The active monitoring will generate 3 levels of data, with the data entered for each “beep” as level 1, nested within the level 2 “day” level, which is nested within the level 3 subject level. Because the PANSS and CDSS measure participants’ symptoms for the past week, and to minimize the impact of missing data, the subject level mean score of the first week will be used to calculate the association between active monitoring items score and relevant symptom domain scores of the PANSS and CDSS at the week 1 follow-up assessment to evaluate validity. The significance level for the study will be set to .05. Cronbach alpha will be used to calculate the internal consistency reliability of the sets of the items of active monitoring. To account for the nested structure of the data, multilevel models will be used to explore the instability of the different constructs across time and patterns of missing data.

The GPS mobility indicators will be extracted from passive monitoring data. The convergent validity of passive monitoring will be calculated by the correlation between GPS mobility indicators and the PANSS negative symptom score. Discriminant validity of passive monitoring will be demonstrated by low correlation between GPS mobility indicators and positive symptoms measured by PANSS.

Qualitative data will be transcribed verbatim in Chinese and then translated to English by the principal researcher. A framework analysis approach will be used based on the protocol by Braun and Clarke [67], which consists of the following 6 phases of thematic analysis: familiarization, transcription, generating initial codes, searching for themes, reviewing themes, and defining and deciding on meaningful themes. Nvivo software (version 12) [68] will be used to manage the qualitative data.

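### Inpatients are not excluded and the GPS rules treat a ward as home, so any inpatient in the rated week could inflate or dilute the exploratory GPS–PANSS correlations

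*Protocol article*

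**What the plan says.** **Who can enter.** The inclusion criteria (Textbox 1) ask for care from the hospital and continued support over the next 5 weeks. They do not mention inpatient or outpatient status. The exclusion criteria remove people whom the treating clinician judges unsafe to take part, for example because they are unstable, but admission itself is not an exclusion. Study Setting describes both kinds of care: "The hospital has 800 beds, an average 5000 inpatient admissions per year, and over 1200 daily outpatient visits".

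**How GPS data become indicators.** Under Passive Monitoring, "locations will be clustered as “unique” if a person spent at least 30 minutes within a 200-meter radius", and "distance changes of GPS data points in the same location cluster will be considered as zero". Home is set by the night-time mode: "Home location will be determined by selecting the mode of location clusters during the night (ie, 9 PM to 6 AM". No exception is stated for nights in hospital.

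**How location is self-reported.** Table 1 under Active Monitoring gives hospital as an answer separate from home: "At home; at work; at school or other educational setting; in hospital; in vehicle". The purpose of these items is also stated: "Contextual questions were added to understand the context of participant responses and to validate GPS data".

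**How the indicators are used.** In the Statistical Analysis Plan section, "The convergent validity of passive monitoring will be calculated by the correlation between GPS mobility indicators and the PANSS negative symptom score", and a low correlation with PANSS positive symptoms is to show discriminant validity. The Validity section labels this work exploratory: "An exploratory analysis will also be conducted to understand the association between mobility indicators". That section then gives a validity threshold of a significant Spearman rho above 0.35.

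**The concern.** The indicators are meant to reflect how much a person chooses to move about, which the article links to apathy, avolition, asociality and anhedonia. For someone living on a ward, the same indicators are fixed largely by the admission. If such participants are pooled with people living at home, two errors are possible.

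- **Inflation.** If inpatients score higher on PANSS negative, high home time goes with high scores even when mobility says nothing about negative symptoms among people in the community. If they also score higher on PANSS positive, the discriminant check is distorted in the same way.
- **Dilution.** If inpatients are equally or less severe, their extreme values weaken an association that is present among outpatients.

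A reader given only the pooled correlation could not tell which had happened, or whether either had. Passive monitoring is one of the app's two core functions, so its validity result is likely to be used in deciding whether GPS is kept.

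**Working it through.** **Step 1: apply the stated rules to a participant on a ward.** Assume that the ward is the place slept in on most nights and that daytime movement stays within one 200-metre cluster.
- Night-time mode = ward, so home = ward.
- Home time = time in that cluster, near its maximum.
- Distance = 0 within the cluster, so near its minimum.
- Number of clusters = about 1.

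**Step 2: which criterion binds.** The article gives no power or error figure for the GPS analysis, so there is none to reproduce. It does give n=40, alpha .05 (two-sided assumed) and the threshold rho>0.35. The critical rho is t/√(n−2+t²) with t(0.975, 38)=2.024: 2.024/√(38+4.10) = 0.312. Since 0.35 exceeds 0.312, the 0.35 threshold decides.

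**Step 3: size of the effect.** The number of inpatients and their difference in severity are not in the article, so both are assumptions: 0, 4, 10 or 20 of 40, and −0.5 to +1 SD on PANSS negative. Other participants are drawn as bivariate normal with correlation r between home time and PANSS negative. Inpatients have home time near the ceiling (mean +3 SD, spread 0.2 SD), unrelated to symptoms. There were 20,000 simulated studies per setting. Entries are P(pooled rho>0.35).

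| Outpatient r | Inpatient shift | 0 inpatients | 4 | 10 | 20 |
|---|---|---|---|---|---|
| 0 | 0 | 0.012 | 0.013 | 0.013 | 0.012 |
| 0 | +0.5 SD | 0.012 | 0.035 | 0.102 | 0.182 |
| 0 | +1 SD | 0.012 | 0.083 | 0.351 | 0.630 |
| 0.5 | −0.5 SD | 0.833 | 0.378 | 0.050 | 0.002 |
| 0.5 | 0 | 0.833 | 0.612 | 0.291 | 0.068 |
| 0.5 | +0.5 SD | 0.833 | 0.786 | 0.694 | 0.434 |
| 0.5 | +1 SD | 0.833 | 0.902 | 0.938 | 0.873 |

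A Fisher-z check on the 0.833: (atanh 0.5 − atanh 0.35)/√((1+0.5²/2)/37) = (0.549−0.365)/0.174 = 1.05, which gives 0.85.

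The r=0 rows apply equally to PANSS positive, with the shift read as a shift in positive symptoms.

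**Step 4: reading the table.** With no inpatients nothing changes. With no true association and equal severity, no false pass is created. With a true association and inpatients 1 SD more severe, nothing is hidden. Harm needs a particular combination, but 4 inpatients of 40 are enough for a visible effect in several rows.

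**Step 5: what the fix costs in precision.** If 10 inpatients were dropped, n=30 and the critical rho is 2.048/√(28+4.19) = 0.361, so significance now binds. With r=0.5: (0.549−0.378)/√(1.125/27) = 0.171/0.204 = 0.84, a chance of about 0.80. This compares with 0.85 for 40 outpatients by the same approximation, and with 0.291 for the simulated pooled analysis of 30 outpatients and 10 inpatients of equal severity.

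**The case against.** **No inpatient is documented.** This stands. Study Setting mentions over 1200 outpatient visits a day alongside the beds. The recruitment route (contact details taken, a phone call after at least 48 hours, then an arranged meeting) and the requirement of clinical stability lean towards outpatients. The hospital answer in Table 1 fits an outpatient visit just as well. None of this bars a stable inpatient.

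**A short admission does not make the ward home.** This also stands. Home is the mode. Over a seven-night window with two sleeping places, the ward needs at least 4 nights. With fewer, the real home is kept, ward time becomes a separate cluster and home time falls, which is the opposite distortion. Ceiling values also assume little leave from the ward. The PANSS for this comparison is taken at week 1 (Data Collection), so later admissions may not matter.

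**The analysis is exploratory, in a feasibility study.** True, and it limits the weight of the point. Even so, the Statistical Analysis Plan section presents the result as convergent and discriminant validity.

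**The contextual items can clean the data.** They make hospital time partly detectable, but no stated rule uses them to drop or reclassify it.

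**This is a condensed article that cites an extraction procedure.** A hospital rule may exist there. However, the article does state the home rule, and as stated that rule misclassifies a group whom the eligibility criteria admit. That is more than an omitted detail.

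**Conclusion.** The point holds as a conditional one. The stated eligibility and GPS rules together label a ward as home for any participant who spends most nights there, and no stated step corrects it. If there were inpatients in the week 1 window, the pooled correlations could be inflated or diluted. On the assumed inputs, the chance of passing 0.35 moves from 0.012 to between 0.035 and 0.351 with 4 to 10 inpatients who are 0.5 to 1 SD more severe and no outpatient association. It moves from 0.833 to 0.612 (4 inpatients) or 0.291 (10) with equal severity and an outpatient correlation of 0.5. These sizes rest on assumed numbers, assumed shifts, near-ceiling home time and use of the first week's GPS data. With no inpatients the effect is nil.

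A reader might infer that the study's mobility indicators measure admission rather than negative symptoms, or that the GPS validity question cannot be answered. The article does not support either reading: it gives neither the number of inpatients nor their difference in severity, and the distortion concerns only participants or days on a ward. The change is still worth making, because it is cheap and removes a bias of unknown direction.

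**What to change.** The article says that the GPS indicators will be extracted, so the rule can still be set before the analysis.

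1. Do not allow a hospital ward to be assigned as home.
2. Base the main GPS–PANSS correlations (negative and positive) on days spent living in the community or, more simply, on participants not admitted during the rated week.
3. Identify hospital time from the hospital answer to the location question, from care setting at enrolment and, where available, from EHR admission and discharge dates.
4. Report how many participants and days were excluded, including zero if that is the case.
5. Show the all-days, all-participants result as a sensitivity analysis.

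**Cost.** It needs one data-handling rule. The GPS analysis loses participants or days if some were inpatients; for 10 of 40 the loss of precision is modest (Step 5). The EHR section lists the number of hospitalizations, not their dates, so a small extra extraction may be needed. If no one was admitted, one sentence saying so is enough.
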